### 8.3 Psychometric Data Analysis

**8.3.1** We would like to recruit sample size of 100 to 150 to ensure stability of person and item calibrations in the psychometric data analysis. (Linacre, 1994) To enable item calibrations on the PROMs to within ½ logit requires 100 to 150 participants for confidence intervals of between 95% and 99% this will help us ensure that we have sufficient power to test out the psychometric validity of the PROMs being used in the SMOOTH study.

Data will be analysed using Classical Test Theory (CTT) and Rasch Analysis to capture change over time and comparisons using known groups validity. A small cohort of approximately 60 people will be asked to complete the measure 2 weeks apart to evaluate for test-retest reliability.

Rasch Analysis to identify psychometric validity of measures:

**8.3.2 The Rasch Model**

The Rasch model can be utilised to examine the psychometric properties of the BBSIP that cannot always be identified using traditional analysis such as CTT. The Rasch model discloses anomalies in the data and the extent to which individual items in the BBSIP capture a unidimensional construct and therefore the extent to which summation of items from the PROMS are legitimate (19).

**8.3.2.1 Rasch Analysis**

Rasch analysis is an iterative process that will identify anomalies in the data and the extent to which the PROMs data conforms to the Rasch model and therefore the extent to which the instruments are unidimensional. Fit will be established using a variety of indicators and fit statistics. The Rasch Unidimensional Measurement Model software (RUMM2030) will be used to analyse the PROMs. (RUMMLAB, 2018, Andrich, 1988)

**8.3.2.2 Scoring Categories**

Rasch analysis can examine the scoring categories of the instruments and establish the extent to which scoring categories capture increasing/decreasing levels of the underlying construct. Where affirmation of scoring categories by respondents follows a logical sequence then Rasch Andrich thresholds appear ordered. Rasch Andrich thresholds are the points between adjoining categories where the probability of affirming either category is 50/50, when responders’ perceived level of health is equidistantly captured by adjoining categories. Where there is agreement with this expected response hierarchy, thresholds appear ordered, disordered thresholds are observable as a lack of consistency. Disordered thresholds can suggest poorly defined or redundant scoring categories and therefore conceptual distinctions between categories maybe imprecise. Responders then find it difficult to assign a category to their perceived health status.

**8.3.2.3 Targeting**

Targeting will be established by examining the extent to which distributions of participants perceived health status and levels of health identified by the PROMs are analogous.

**8.3.2.4 Person Separation Index**

The person separation index (PSI) is conceptually equivalent to Cronbach’s Alpha. It identifies the extent to which the instrument is able to discriminate between groups with different health states and the precision of the estimate for each person.

**8.3.2.5 Tests of fit**

Individual tests of fit for each person and item will reflect the difference between responders observed and expected responses if data fits the Rasch model. RUMM2030 automatically clusters responders into equivalent size groups (class intervals) according to their overall level of perceived health. A number of statistics utilise these class intervals including χ^2^ statistics and residual values (±2.5). Residuals are summations of individual item or person deviations from expected fit to the Rasch model, standardised as a z-score. Residual scores between ± 2.5 indicate adequate fit to the Rasch model. A significant chi-square suggests data do not fit the Rasch model.

**8.3.2.6 Differential Item Functioning**

Differential item functioning (DIF) is a form of item bias that can affect fit to the model. DIF manifests itself when responses to individual items by sample sub-groups (e.g. gender or age group) are inconsistent with their overall perceived level of health. DIF will be identified using ANOVA and statistically significant probability (*p*<.05, or a Bonferroni corrected level). DIF for gender, age group and additional identified clinical group categories e.g. type of burn injury will be examined.

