**2.2.2 Secondary endpoints**

The secondary endpoints include: subjective (BBSIP, POSAS and mVSS) scores and objective assessment of the areas of interest on Months 3, 6 and 12 after first laser treatment. Objective assessment includes; 3D (Vectra H1) photography, scar thickness and density using Ultrasound (Derma scan cortex Denmark), pliability (Cutometer) and scar colour and pigmentation using DSM Colorimeter .

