The study also identified that only two measures had been developed with patient input, in line with FDA recommendations, and only one that was scar specific. The Brisbane Burn Scar Impact Profile (BBSIP) will be used in this study to evaluate its psychometric properties in patients receiving laser therapy. The tool will be validated in this population using Classical Test Theory (CTT) and Rasch Analysis, alongside a range of questions to establish the ability of the PROM to differentiate between groups e.g. improved scar tissue, no change or worse scarring and clinical data.

BBSIP data will be collected in clinics as illustrated in the diagram below (Figure 1), and patients will be given the option to complete a paper and pencil version of the measure or an online version using smart survey. Participants will also be asked to sign a consent to contact form to enable a member of the CPROR research team to analyse their data and have access to information from the demographic questionnaire for use in the psychometric analysis.

Participants to the study will be recruited at the outpatient clinics from the Queen Elizabeth Hospital Birmingham and the Morriston Hospital, Swansea.

Patients deemed suitable for the research trial and who meet the inclusion and exclusion criteria will be assessed for capacity before proceeding with the informed consent process.

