**5.2.1** **PROMS Sub-Study**

Patients attending routine clinical appointments will be asked if they are willing to complete copies of the BBSIP and POSAS plus a consent form and demographic questionnaire to enable psychometric validation of the PROMs. Inclusion criteria will be any patients with sufficient understanding of written English to complete a PROM. Exclusion criteria will be patients with insufficient written English to complete PROMs. Data will be collected over a two-year period in line with the laser study data collection time points. Patients recruited for the SMOOTH study will not be taking part in the PROMS sub-study since the same data will be collected in the SMOOTH study. SMOOTH patients will only be asked to sign one consent form to take part in the study and will complete the PROMs as part of the SMOOTH study.

The PROMS PIS and validation consent form will be used to recruit additional patients who are not part of the SMOOTH study to test the psychometric validity of the BBSIP and POSAS. As only 60 patients will be recruited to the SMOOTH study and this is not sufficient to test the psychometric validity of the PROMs being used. The sub-study will be carried out in routine clinics alongside the SMOOTH study. Data will be collected at two time points and patients will be asked to complete the known groups PROM validation questionnaire at the second time point. This allows the investigators to see if changes captured by the PROMs reflect participants perceptions of change in their scar tissue.

The investigators have both ethical and legal responsibility to ensure that each subject being considered for inclusion in this study is given a full explanation of the protocol and has demonstrated their understanding. This shall be documented on written informed consent forms

An ethically approved written informed consent will be signed and dated by: the subject (or the subject’s legally authorized representative), the individual obtaining consent, and by any other parties required by the ethics committee. This will be completed after the appropriate and essential information has been provided to the participant) and has been fully explained by the investigator (or designee), and it is felt that the participant (or the participants’s legally authorized representative) understands the implications of participating in the study.

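### Rasch scores are meant to capture change over time, but time point is not among the factors listed for the item-bias (DIF) check

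*Protocol*

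**What the plan says.** **Purpose.** Section 8.3 states: "Data will be analysed using Classical Test Theory (CTT) and Rasch Analysis to capture change over time and comparisons using known groups validity". The secondary objectives in section 2.1 ask whether the BBSIP soundly measures improvement in scarring and its effect on quality of life.

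**Repeated completion.** For the PROMS sub-study, section 5.2.1 says "Data will be collected at two time points", with a questionnaire on perceived change at the second. In the main study, section 2.2.2 sets the subjective scores at "Months 3, 6 and 12 after first laser treatment", and Appendix A adds a baseline completion.

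**Item-bias check.** Section 8.3.2.6 names the factors: "DIF for gender, age group and additional identified clinical group categories e.g. type of burn injury will be examined". The test is ANOVA at p<.05 "or a Bonferroni corrected level".

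**Use of the scores.** Section 8.3.2.8 allows logit scores to be used in place of raw scores if the data fit the model.

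**Form of completion.** Section 3.1 says of the BBSIP that "patients will be given the option to complete a paper and pencil version of the measure or an online version using smart survey".

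**The concern.** A person's Rasch estimate is read from the total score using fixed item locations. When two occasions are compared, the method assumes that a given level of scar impact produces the same expected answer to each item both times. If patients come to rate one item differently with experience, the total moves and the model reports a change in the person, although the scar has not changed.

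The listed DIF factors all compare different people: men with women, age groups, types of injury. None compares the same people at two times. The open-ended part of the list extends only to clinical groups, and a visit is not a clinical group. So the invariance on which a change score rests is the one that the list leaves out.

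At stake is the secondary objective on the BBSIP. Unexamined drift could make the questionnaire look more responsive, or less, than it is.

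**Working it through.** **Inputs from the protocol.** Psychometric sample 100 to 150 (8.3.1). Six items in each POSAS scale, ten steps each (7.3.4.2). The BBSIP is described only as having seven parts (7.3.4.3).

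**Assumptions.** Item drift d = 0.5 to 1.0 logit; scale lengths of 6, 20 and 60 items, to span what the BBSIP might be. The protocol gives no figure for either.

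**1. The plan's own figure.** The only number in this part of the plan is the 100 to 150 needed to calibrate items to within half a logit. For a dichotomous item endorsed with probability p, N = (z*c/0.5)^2 with c = 1/sqrt(p(1-p)).
- At 95% and p = 0.8: c = 2.5 and N = (1.96*2.5/0.5)^2 = 96.04, so 97.
- At 99%, N = 150 corresponds to p of about 0.77.

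The stated range is therefore plausible, although p is not given. The present point does not depend on it.

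**2. Bias from drift.** If an item shifts by d, its expected score moves by about d times that item's information. Dividing by the information of the whole scale gives the shift in the person estimate. With k of m items of equal information drifting, this is k*d/m.

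| Drifting items | d = 0.5 | d = 1.0 |
| --- | --- | --- |
| 1 of 6 | 0.5/6 = 0.083 | 1/6 = 0.167 |
| 1 of 20 | 0.025 | 0.050 |
| 1 of 60 | 0.008 | 0.017 |
| 20% of items | 0.10 | 0.20 |

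**3. Check without the approximation.** Expected scores were inverted under a partial-credit model. Item parameters were held at their first-occasion values, true change was zero, and persons were distributed about N(0,1), truncated at plus or minus 1.5. The shifts for d = 0.5 and 1.0 were 0.086 and 0.163 (1 of 6), 0.026 and 0.051 (1 of 20), and 0.009 and 0.017 (1 of 60). With 20% of items drifting they were about 0.10 and 0.20 for scales of 10 to 60 items. Six ten-step items gave 0.087 and 0.161. The approximation holds.

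**4. Could the check detect drift?** Treating the two occasions as independent, power for one item drifting 0.5 logit at two-sided 0.05 is about Phi(0.5/(c*sqrt(2/N)) - 1.96). With c = 2 to 3:
- N = 100: Phi(1.77 - 1.96) = 42% down to Phi(1.18 - 1.96) = 22%.
- N = 150: Phi(2.17 - 1.96) = 58% down to Phi(1.44 - 1.96) = 30%.

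A Bonferroni level lowers these. A p-value alone is therefore a weak screen, and the size of the DIF should be reported with it.

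**5. Paper versus online.** A form effect biases mean change only through the net share of patients who switch form between visits. For one of six items at 0.5 logit: 0 with no net switching, 0.087*0.2 = 0.017 at 20%, and 0.087 if everyone switches.

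**The case against.** **It belongs in the analysis plan.** The full set of DIF factors is often left to a later document, section 8.3.2.1 calls Rasch analysis iterative, and nothing forbids a test by time. This has force: the list is incomplete, not contradictory. But the protocol chose to name its factors, test and threshold, and the list does not serve the aim stated in 8.3.

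**Other safeguards exist.** Section 5.2.1 compares PROM change with perceived change, section 8.3 has a retest of about 60 people two weeks apart, and classical methods run alongside. These are real but partial. The first works at the level of the whole score, the second concerns reliability over a short interval, and the fit statistics in 8.3.2.5 group people by overall level and not by occasion. None separates drift from true change item by item.

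**Time DIF may be genuine.** Laser could improve itch or colour more than other aspects, and that would also appear as time DIF. Routinely splitting or removing such items could discard real improvement. This objection stands and shapes the fix.

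**Stronger readings to avoid.** A reader might infer that drift is occurring and is being counted as scar change; the protocol gives no evidence either way. A reader might also turn the bias into a collapse of confidence-interval coverage. With an assumed SD of change of 1 logit and N = 100 to 150, the standard error is 0.08 to 0.10. A six-item scale then gives coverage of about 87% down to 48%. The lowest figure needs the shortest scale, the largest drift and the largest N together. One of 20 items gives about 94% to 91%. The SD and the number completing both occasions are not stated, and section 8.3 describes no such interval. Nor does the choice of paper or online by itself bias change; that needs net switching. Section 3.1 offers the choice for the BBSIP in the main study, and section 5.2.1 does not repeat it for the sub-study.

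**Conclusion.** The point holds as a minor one. Change over time is a stated use of the Rasch analysis, and the item stability that this use requires is not checked by time point. The consequence is conditional on drift. One drifting item would matter on a scale as short as six items (about 0.08 to 0.17 logit) and hardly at all on one of 60 (about 0.01 to 0.02). Several items drifting in the same direction would matter at any length: about 0.10 to 0.20 logit if one fifth do so. These sizes rest on an assumed drift of 0.5 to 1.0 logit, and the BBSIP item count is not in the protocol.

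The scope is a secondary psychometric objective in a pilot whose analysis is descriptive (section 8.2). The laser versus control comparison on the primary histological endpoint is untouched.

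**What to change.** In section 8.3.2.6:

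- Add time point (first versus later completion) to the DIF factors.
- Allow for repeated completions by the same person, for example by calibrating items on one completion per person.
- Report DIF size in logits as well as p-values.
- Report change scores with and without items showing material time DIF, as a sensitivity analysis. Do not split items automatically, since such DIF may be real item-specific improvement.
- Optionally, record paper or online at each completion and examine it as a secondary DIF factor.

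**Cost.** The time-point check uses data already planned; recording the form needs one extra field. There will be a few more tests, and power to detect drift in a single item stays modest at 100 to 150 participants, so a null result should not be read as proof of stability.

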**8.3.2.7 Item Independence**

Item independence is an underlying principle of the Rasch Model. Response dependency occurs when a person’s response to one item determines the response to another item and therefore responses are not independent of each other. Residual correlation metrics (<0.2 above the average residual correlation) will identify if response dependency is an issue.

Once the ‘Rasch factor’ is extracted, leftover residuals should not contain any patterns in the data. A principal components analysis (PCA) of the residuals will detect if multi-dimensionality is an issue.

**8.3.2.8 Logit transformation**

If data from the individual measures fits the Rasch model, patient and item parameter estimates are then positioned on the same log-odds units (logits) scale, although as independent parameters. This allows for a linear transformation of the raw scores to be utilised. Therefore, estimates of a patient’s perceived perceptions relating to their scars or impact of scarring on quality of life can be derived from the PROMs with confidence.

**8.3.2.9 Modify Instrument**

Based on the results of the psychometric validation of the PROMS, modifications may be required to ensure that the PROMs capture the best quality data.

## 8.4 Data Monitoring & Interim Analysis

Data analysis will be performed on a 3 monthly basis to ensure that high quality, relevant data is being generated. If some blood sampling is felt of little benefit or shows little correlation this may be discontinued. This will ensure that patients are not undergoing unnecessary blood sampling. The decision to remove a specific test will be made following collaboration with all Investigators

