## 2.2 Study Endpoints

**2.2.1 Primary endpoints**

The primary endpoint is to assess the effect of the ablative carbon dioxide laser therapy via histological assessment of the hypertrophic scarring and in particular using novel methodology to detect the number of senescent cells and the subpopulation of fibroblast 6 months after the third laser treatment.

Scars will be assessed histologically (5mm punch biopsy) to assess dermal and epidermal thickness, collagen structure and orientation, elastin density and structure. Immunostaining will examine possible scar biomarker, proportion of senescent cells and the proportion and sub-population of fibroblasts following treatment.

To identify novel markers associated with scarring and tissue regenerative capabilities such as markers of cellular senescence and DNA damage, for example p16 and ɣH2Ax and other biomarkers including: micro RNAs, TGF-beta, decorin, VAP-1, MMPs, PDGF, adiponectin, etc.

To identify expressions and markers both in blood and tissue samples that influence scar formation, wound healing and variables of scar behaviour in response to CO_2_ laser therapy. This will include; pro and anti-inflammatory cytokines, scar biomarkers and markers of cellular senescence, for example mmp.

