## Number of Participants

A total of sixty (60) participants will be recruited to the study over the period of 2 years. Civilian patients will be recruited from the recently established Advanced Scar Management clinic at University Hospital Birmingham and The Welsh Centre for Burns and Plastic Surgery, Morriston Hospital, Swansea. Veterans will be recruited in collaboration with the CASEVAC Club volunteers.

- 1. **Expected Duration of Study**

We anticipate that the recruitment and follow up of 60 patients across both sites will be 2 years or after the 6-month follow-up of the last patient.

- 1. **Inclusion Criteria**

1. Adult patients aged ≥ 16years
2. Patient with symptomatic hypertrophic scarring as a result of deep dermal or full thickness burns/trauma.
3. Trauma or Burn sustained more than 12 months prior to recruitment.
4. Treatment area to be ≥25cm^2^ confluent scarring with a comparable control scar on limb or trunk

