# DATA MANAGEMENT & STATISTICS

## Determination of Sample Size

**8.1.1 Laser Treatment and Standard of Care**

Following recommendations for pilot studies, 30 patients or more are typically required to gain estimates of the parameters needed for sample size estimation. No formal sample size calculation has been performed as a result. We have allowed for a 20% drop-out and possible loss to follow-up. We therefore aim to recruit 60 participants in total. This will also allow the recruitment and retention rates to be estimated with 95% confidence interval maximum widths of 20% and 25% respectively.

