The primary analysis for the trial will occur once all participants have completed the 12 month assessment and corresponding outcome data has been entered onto the trial database, validated as being ready for analysis, and the database locked. This analysis will include data items up to and including the 12 month assessment.

For the secondary outcome data about the biomarkers of the scar response to laser therapy the various cellular and molecular variables will be examined for relationships to scarring using logistic regression. Further longitudinal analysis to identify potential drivers of a positive response will be done using linear mixed-effects modelling.

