# PUBLICATION POLICY

The findings from the research trial will be published at various stages of the trial in relevant medical journals and presented at medical conferences.

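### Section 8.4 lets a blood marker be dropped mid-trial for showing little correlation, which selects markers on the association the study is meant to estimate

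*Protocol*

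**What the plan says.** Section 8.4 (Data Monitoring & Interim Analysis) sets the timetable: "Data analysis will be performed on a 3 monthly basis to ensure that high quality, relevant data is being generated". It then gives the ground for stopping: "If some blood sampling is felt of little benefit or shows little correlation this may be discontinued". On who decides, it says: "The decision to remove a specific test will be made following collaboration with all Investigators". The stated purpose is to spare patients unnecessary blood sampling. Section 8.4 does not say what the marker is to be correlated with, how weak a correlation counts as little, how many patients must be in hand, or whether stopped markers are reported. Section 7.4.1 adds that the list of laboratory tests may change as data are analysed.

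The role of the blood markers is set out elsewhere. Under the primary endpoints, section 2.2.1 lists this aim: "To identify expressions and markers both in blood and tissue samples that influence scar formation". Section 8.2 then relates the cellular and molecular variables to scarring by logistic regression and linear mixed-effects models.

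**The concern.** A rule that stops a measurement because its interim correlation with outcome is small uses the very quantity the final analysis will report. Two consequences follow.

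- With few patients an observed correlation is mostly noise, so a marker with a real but moderate association can be discarded by bad luck.
- Markers that pass have, on average, been lucky early. Their final estimates include those early patients and are therefore too high.

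This pilot is meant to inform a larger trial and to suggest biomarkers of response, so both errors would carry forward. If blood stops being drawn for a marker, the later samples cannot be recovered. Samples already banked can.

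**Working it through.** Section 8.4 contains no figure to reproduce. The check asks what the rule could do if applied.

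**Inputs from the protocol.** Looks every 3 months (8.4). Accrual: "A total of sixty (60) participants will be recruited to the study over the period of 2 years". Attrition: "We have allowed for a 20% drop-out and possible loss to follow-up", so 60 × 0.8 = 48 completers. Scar assessments at baseline, month 3, month 6 and 6 months after the third treatment, i.e. about month 12 (7.5.4 to 7.5.6, Appendix A).

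**Assumptions not in the protocol.** Even accrual; correlation means correlation with scar response; cut-offs of |r| < 0.1, 0.2 or 0.3; true correlations of 0, 0.3 or 0.5; bivariate normal data; automatic dropping at the first look below the cut-off; and the same marker–outcome pair at interim and final analysis.

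**Step 1: patients available.** 60 / 8 quarters = 7.5 per quarter. Scar data at 3 months lag enrolment by one quarter. Before dropout, patients with 3-month data number 0 at month 3, 7.5 at month 6, 15 at month 9, 22.5 at month 12 and 30 at month 15. For the final assessment there are none until after month 12, then 7.5 at month 15, 15 at month 18 and 30 at month 24. A small-sample decision is therefore possible from about the month-6 look, not the first.

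**Step 2: precision of r.** By Fisher's z, 95% limits are tanh(atanh(r) ± 1.96/√(n − 3)). For a true correlation of zero:
- n = 7: tanh(1.96/2.000) = 0.75
- n = 15: tanh(1.96/3.464) = 0.51
- n = 30: tanh(1.96/5.196) = 0.36

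An observed r of 0.4 at n = 8 gives tanh(0.424 ± 0.877), i.e. −0.42 to 0.86.

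**Step 3: chance of dropping and size of survivors.** Simulation with 40,000 runs per setting, survivors carried to n = 48. Figures repeat between runs to about half a percentage point and 0.01 in r. Each cell gives cut-offs 0.1 / 0.2 / 0.3.

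| True r | Looks at n = | Dropped | Mean final r in survivors |
|---|---|---|---|
| 0.3 | 7 | 13 / 26 / 38% | 0.30 / 0.31 / 0.32 |
| 0.3 | 30 | 12 / 27 / 49% | 0.32 / 0.35 / 0.38 |
| 0.3 | 7, 15, 22, 30 | 33 / 54 / 72% | 0.34 / 0.37 / 0.40 |
| 0.5 | 30 | 1 / 3 / 10% | 0.50 / 0.50 / 0.51 |
| 0.5 | 7, 15, 22, 30 | 12 / 22 / 36% | 0.51 / 0.52 / 0.53 |

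Hand check of one cell (true r 0.3, n = 30, cut-off 0.2), with atanh(0.2) = 0.203 and atanh(0.3) = 0.310: Φ((0.203 − 0.310) × 5.196) − Φ((−0.203 − 0.310) × 5.196) ≈ 0.289 − 0.004 = 0.285. The simulation gives 27%.

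**Step 4: no selection.** Without dropping, mean final r is 0.297 and 0.496 for true values of 0.3 and 0.5, so it is essentially unbiased.

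**Step 5: null markers.** Four looks leave about 35%, 14% and 5% of markers with no association. Of those left, 11%, 19% and 34% exceed the nominal 95% limit at the end, instead of 5%. The total of such false signals does not rise (0.35 × 0.11 ≈ 0.04), but the survivors look more convincing than they should.

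**The case against.** Section 8.4 says a test may be discontinued, after all investigators have collaborated; it does not impose an automatic rule. It names no correlate. The study is a descriptive pilot without formal testing. Section 8.2 calls the biomarkers secondary outcome data, although 2.2.1 lists them under the primary endpoints. Aliquots are banked at −80 °C (7.4.2), so a marker whose assay is stopped could be measured later. If whole tubes or visits were dropped, patients would be spared a real burden, since blood is taken at five visits.

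Much of this limits the size of the problem. The percentages are illustrations, and the loss is permanent only for blood never drawn. An interim correlation with 3-month scarring would also bias a final analysis of a later outcome less than the table shows. The objection does not remove the defect. Selection distorts estimates and confidence intervals, which are this pilot's output, whether or not tests are done. Stopping one assay spares no needle while other markers use the same serum and plasma tubes.

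A reader might infer more than the documents support:

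- **Blinding.** Section 5.4.3 blinds assessors and analysts to which site was lasered. One systemic blood sample per visit cannot reveal that.
- **Conflict with section 8.2.** The condition that data be "validated as being ready for analysis, and the database locked" applies to the primary analysis only. An interim data review does not contradict it.
- **Publication policy.** It says "The findings from the research trial will be published at various stages of the trial", but not that marker–response or laser-versus-control results will appear before lock.
- **Dropping from the first look.** At month 3 there is almost no post-treatment scar response to correlate with.

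**Conclusion.** The concern holds in a limited form. Section 8.4 permits blood markers to be stopped on an undefined, outcome-dependent criterion that overlaps with the association later reported. The direction of the effect is clear: moderate true associations are at risk of being lost, and retained ones are somewhat overstated.

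The size depends on assumptions the protocol does not fix. Over cut-offs of 0.1 to 0.3, a true correlation of 0.3 is lost 12–49% of the time at a single look at 30 patients and 33–72% over four looks at 7 to 30, with survivors averaging 0.32–0.40. For a true correlation of 0.5 the loss is 1–36% and survivors average 0.50–0.53, so strong markers are little distorted. All of this reads the correlation as one with scar response. It is worth correcting before the rule is used, but it does not threaten the laser-versus-control comparison.

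**What to change.** Amend section 8.4 as follows:

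- Delete little correlation as a ground for stopping.
- Allow a blood test to be removed before database lock only for assay or sample-quality reasons judged without scar outcome or allocation, for example a marker undetectable in most samples or failing quality control.
- Keep drawing and banking serum and plasma while any marker still needs them.
- Require every marker measured to be reported, including any that were stopped, with the reason.

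The provision in 7.4.1 for changing the test list should refer to the same conditions. The cost is a wording amendment plus some storage and assay work on markers that turn out to be uninformative.
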